Wet AMD is preceded by dry AMD, which is characterized by a gradual degeneration of macular cells and the presence of lipid deposits beneath the retina both contributing to central vision loss. According to the global percentage of dry AMD progression to wet AMD, around 10–15% of patients with dry AMD progress to the wet form (4). Although there is no cure for dry AMD, the pipeline of new treatments to slow its progression is expanding. Once wet AMD is established, anti-VEGF therapy is intended to manage rather than cure wet AMD with most patients experiencing sight loss over time despite regular treatment. Preventing conversion, therefore, has better prognostic value for sight. A number of modifiable risk factors have been found to be effective in slowing AMD progression, such as smoking cessation, and dietary and nutraceutical supplements. In this respect, nutraceutical treatments might limit eye disease progression (5, 6). Among them resveratrol has emerged as a promising agent for mitigating retinal damage (7, 8). Some therapeutic agents have also been licensed for eyes with dry AMD including complement factor inhibitors, which, on the other hand, are only available for individuals with late-stage dry AMD (9). There exists a need for drugs for earlier stages of dry AMD that effectively reduce the risk of progression. Targeting oxidative stress and chronic inflammation might represent an effective treatment as their complex interplay plays a key role in retinal diseases (10).

Potential concomitance between AMD and OAB gave rise to the possibility of investigating whether a therapy that efficiently counteracts OAB may also act on dry AMD progression to wet AMD. As for wet AMD, the global prevalence of OAB is expected to increase by 10.6% from 2020 to 2030 with an increasing trend depending on obesity, gender and age (8). While anticholinergics have been the cornerstone of OAB treatment for decades, their use has consistently been challenged by issues related to side effects and lack of bladder selectivity (11). In particular, there is indication that eye diseases including glaucoma (12) and dry eye disease (13) might occur as side effects of anticholinergic drug administration in OAB patients.

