### Study design and participants: inclusion, exclusion and drop out criteria

2.1

We planned an observational double arm non-randomized study in two centers to compare the safety and efficacy of either mirabegron (50 mg/day) or solifenacin (5 mg/day) in OAB patients. The protocol provides that ophthalmologists will be blinded regarding which patients have been treated with both drugs. We planned to enroll 312 subjects aged between 50 and 80 years with a diagnosis of early or moderate dry AMD, according to ARDS classification, and OAB. The patients will be enrolled at the Department of Ophthalmology of the University of Lublin, Poland and the University of Naples Federico II, Italy from December 2025 to October 2026. All patients will be followed for a 12-month period. The study will be conducted in compliance with the tenets of the Declaration of Helsinki, accepted by the local Ethics Committee, protocol numbers 2025a45673 at the University of Naples Federico II, Italy and KE-0379/97/2025 at the University of Lublin, Poland.

All study participants will provide written informed consent prior to enrollment and for the use of their clinical data for scientific research in an anonymized manner. Inclusion and exclusion criteria are summarized in Table 1.

**Table 1 tab1:** Inclusion and exclusion criteria.

Inclusion criteria
Age 50–80-year-old
Patients with early or moderate dry AMD in one or both eyes
Patients with wet AMD in the other eye
OAB treated for at least 6 months with either mirabegron or solifenacin
BCVA > 65 EDTRS letters
Exclusion criteria
Any contraindication to β-agonists or anticholinergics
Allergy to β-agonists or anticholinergics
Uncontrolled hypertension; tachycardia; atrial fibrillation; long QT or concomitant treatment with drugs that cause lengthening of the QT interval
Patients exposed to experimental drugs other than mirabegron or solifenacin, complement factor inhibitors, photobiomodulation therapy, transscleral lutein iontophoresis therapy or recent surgery (e.g., 3 months)
Recurrent urinary infections
Renal or hepatic failure
Signs of ocular inflammation
Any other ophthalmic diseases such as dry eye, glaucoma, acute or chronic uveitis, advanced cataract
Pregnancy

AMD, age-related macular degeneration; OAB, overactive bladder; BCVA, best corrected visual acuity; EDTRS, early treatment diabetic retinopathy study; QT interval, the time from the start of the Q wave to the end of the T wave in an electrocardiogram.

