All statistical analyses will be done using Python in the Google Colab cloud computing environment and/or SPSS (version 31). The primary confirmatory timepoint will be 12 months. To control type 1 error across the pre-specified primary endpoints, *p*-values will be adjusted using the Holm procedure (two-sided). Statistical significance will be set at a two-sided α = 0.05. Analyses will be conducted using exposure-defined (as-treated) and protocol-adherent approaches, rather than randomized intention-to-treat terminology. Continuous variables will be summarized as mean ± standard deviation or median with interquartile range, depending on the data distribution assessed by the Shapiro–Wilk test. Categorical variables will be presented as frequencies and percentages. Baseline characteristics will be described and group balance will be assessed using standardized differences, rather than relying on significance testing of baseline differences.

The primary outcome measures include conversion to wet AMD at 12 months, and outer retinal morphology parameters obtained from SD-OCT and FAF, including RPD type, ONL thickness, ChT, CMT, and FAF changes. These will be analyzed using mixed-effects models to account for repeated measures at T0, 6 months, and 12 months, with fixed effects including treatment group, time, and treatment×time interaction. Robust standard errors clustered by participants will be used to account for correlation between eyes from the same participant. Adjustments will be made for baseline BCVA, age, sex, AMD stage, contralateral wet AMD status (yes/no), and other relevant factors. If assumptions of normality are not met, appropriate non-parametric methods or robust modeling approaches will be used.

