Secondary outcomes will consist of changes in BCVA (ETDRS letters) and mean MS (microperimetry). These will be analyzed using the same modeling method, with post-hoc pairwise comparisons adjusted for multiple testing using the Bonferroni method. Given the non-randomized design, primary analyses will use a pre-specified adjusted model including key baseline prognostic factors (age, sex, baseline BCVA, AMD stage/severity, comorbidities, baseline symptom severity, and contralateral wet AMD status), and results will be reported as effect estimates with 95% confidence intervals. Safety parameters (heart rate, blood pressure, oxygen saturation, need for respiratory support) will be reported as the number and percentage of patients with pathological values, without correlation to other variables. Adverse event rates will be compared using χ^2^ or Fisher’s exact tests.

Extreme values will be checked for plausibility and kept unless classified as data entry mistakes or physiologically unlikely. Missing data will be managed according to their missingness pattern, and sensitivity analyses will be conducted to assess the reliability of the results. Exploratory subgroup analyses will be performed according to AMD stage (early vs. moderate). Sensitivity analyses will exclude participants who stop taking mirabegron before 6 months or require a dose adjustment. In Figure 1, trial flow is schematically represented.

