## Strengths and limitations

3

To date, only oral supplementation with antioxidant agents has been proven to slow the progression of dry AMD (26). Recently, the FDA has approved new drugs, the complement inhibitors Avacincaptad Pegol and Pegcetacoplan, for the late stage of dry AMD, but they have not received the approval from the European Medicines Agency. Intervening in the progression of dry AMD by repurposing OAB therapy would be faster and more cost-effective than developing a new drug because the original drug’s safety, dosage, and toxicity profiles are already known. Whether the mirabegron dosage usually used to counteract urinary incontinence in OAB patients might be potentially effective in preventing retinal vessel proliferation is unknown. It is also unknown how long mirabegron should be administered to see any potential effect on dry AMD progression.

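### The adjustment factors named for this non-randomised two-centre comparison omit centre, smoking and antioxidant supplement use, and the list stays open although the model is called pre-specified

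*Protocol article*

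**What the plan says.** All references are to the protocol article.

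- **Design (section 2.1).** The study is an "observational double arm non-randomized study in two centers". The sites are the "University of Lublin, Poland and the University of Naples Federico II, Italy from December 2025 to October 2026". Table 1 requires "OAB treated for at least 6 months with either mirabegron or solifenacin", so each patient arrives already on one of the two drugs.
- **First list (section 2.3, paragraph on the primary outcomes).** "Adjustments will be made for baseline BCVA, age, sex, AMD stage, contralateral wet AMD status (yes/no), and other relevant factors".
- **Second list (section 2.3, paragraph that opens with the secondary outcomes).** Because treatment is not randomised, the primary analyses are to use a "pre-specified adjusted model including key baseline prognostic factors (age, sex, baseline BCVA, AMD stage/severity, comorbidities, baseline symptom severity, and contralateral wet AMD status").
- **Known influences on progression.** The Introduction describes modifiable factors that slow AMD, "such as smoking cessation, and dietary and nutraceutical supplements". Section 3 says that "only oral supplementation with antioxidant agents has been proven to slow the progression of dry AMD".
- **Other relevant text.** Table 1 restricts neither smoking nor oral supplements. The T0 procedures described in section 2.2 are ophthalmic and do not mention either. Section 2.3 assesses baseline balance by standardised differences and reports conversion by fellow-eye status. No weighting, matching or analysis of unmeasured confounding is described.

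**The concern.** In a non-randomised comparison, covariate adjustment carries most of the burden of making the groups comparable. A factor confounds if it is related both to the outcome and to which drug the patient takes.

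For smoking and supplements, the article supplies the first half itself, because it presents smoking cessation and supplementation as slowing AMD. For centre, the reasoning comes from the design: prescribing habits, case mix and imaging practice can differ between two hospitals in two countries. If the share of mirabegron users also differs between them, a centre difference becomes a drug difference. Centre is known for every patient at no cost, so leaving it unnamed is hard to justify.

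The open-ended item is a separate weakness. It leaves room to settle the covariates after results are seen, which the label of a pre-specified model is meant to prevent.

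At stake are a biased estimate, in either direction, and a type I error rate above the nominal 5%.

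**Working it through.** **1. The two lists side by side**

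| Factor | First list | Second list |
|---|---|---|
| Age, sex, baseline BCVA | yes | yes |
| AMD stage | yes | yes (stage/severity) |
| Contralateral wet AMD | yes | yes |
| Comorbidities (not named) | no | yes |
| Baseline symptom severity | no | yes |
| Open-ended item | yes | no |
| Centre | no | no |
| Smoking | no | no |
| Antioxidant supplements | no | no |

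The second list contains every factor named in the first. The conflict is therefore between an open list and a model called pre-specified.

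**2. The plan's own figure**

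Inputs (section 2.3): 12% vs 3%, two-sided α = 0.05, power 80%. With p = 0.075, the standard pooled formula gives

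n = [1.960 × √(2 × 0.075 × 0.925) + 0.842 × √(0.12 × 0.88 + 0.03 × 0.97)]² / 0.09² = (0.730 + 0.309)² / 0.0081 ≈ 133.3, rounded up to **134 per group**, as stated.

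**3. Events available for adjustment**

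Counting one eye per participant: 134 × 0.12 + 134 × 0.03 = 16.1 + 4.0 ≈ **20 events**. The second list has 7 factors. At one parameter each plus treatment, that is 8 parameters, or 20.1/8 ≈ 2.5 events per parameter. Adding centre, smoking and supplements makes 11 parameters, or 20.1/11 ≈ 1.8. An ordinary regression for conversion cannot carry this. A propensity score models drug received instead, so the smaller group counts: 134 patients for 10 factors, about 13 per factor.

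**4. Could confounding alone produce the planned effect?**

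The planned risk ratio is 0.12/0.03 = 4. E-value = 4 + √(4 × 3) = **7.5**. An omitted factor would need risk ratios of about 7.5 with both drug choice and conversion, beyond the adjusted factors. For comparison, the strongest prognostic contrast cited in section 2.3 is fellow-eye status, at 15.2 vs 3.2 per 100 person-years, a ratio of 4.75.

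**5. Smaller biases, under assumptions that are not in the documents**

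Assume no drug effect, 134 per group and an unadjusted two-proportion test. For a binary factor with risk ratio R, present in 40% of solifenacin and 20% of mirabegron patients, and 12% conversion on solifenacin:

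mirabegron rate = 12% × [1 + 0.2(R − 1)] / [1 + 0.4(R − 1)]

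For R = 2: 12% × 1.2/1.4 = 10.3%. For three independent factors acting in the same direction, the ratio is cubed. For centre, 70% of mirabegron and 30% of solifenacin patients are placed at the lower-rate centre; with rates 9% and 15%, mirabegron is 0.7 × 9 + 0.3 × 15 = 10.8% and solifenacin 0.3 × 9 + 0.7 × 15 = 13.2%.

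Rejection probability = Φ[(d − 1.96·SE₀)/SE₁] + Φ[(−d − 1.96·SE₀)/SE₁], where d is the spurious difference, SE₀ the pooled and SE₁ the unpooled standard error.

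| Assumed scenario | Solifenacin | Mirabegron | Difference (points) | False-positive rate |
|---|---|---|---|---|
| One factor, R = 1.5 | 12.0% | 11.0% | 1.0 | 5.8% |
| One factor, R = 2 | 12.0% | 10.3% | 1.7 | 7.3% |
| One factor, R = 3 | 12.0% | 9.3% | 2.7 | 10.9% |
| Three factors, R = 1.5 | 12.0% | 9.2% | 2.8 | 11.3% |
| Three factors, R = 2 | 12.0% | 7.6% | 4.4 | 23.1% |
| Centres 9% and 15% | 13.2% | 10.8% | 2.4 | 9.3% |
| Centres 6% and 18% | 14.4% | 9.6% | 4.8 | 22.6% |

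These are crude biases. The planned adjustment would remove whatever part runs through the factors already listed.

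**The case against.** - **The planned model already deals with the main driver of risk.** Fellow-eye status is adjusted for and used to stratify reported conversion. A centre gap that came from a different fellow-eye mix would largely disappear. This stands, and it is why the table above shows what is possible rather than what remains after adjustment.
- **The model is not the only safeguard.** Both drugs treat the same indication, eligibility limits age, BCVA, other eye disease and some other AMD treatments, and balance is examined. This stands too. None of these measures, however, deals with centre, smoking or oral supplements.
- **A reader might infer that the article recognises smoking and supplements as confounders.** It does not. It calls them influences on progression and says nothing about how they relate to drug choice. They are plausible confounders, not established ones.
- **A reader might infer that the two lists contradict each other.** The second can be read as filling in the open item of the first. What remains is that the article never says so and does not name the comorbidities.
- **An article condenses, and the baseline form is not shown.** It therefore cannot be said that smoking and supplements go unrecorded. But the article does not leave the covariates to another document. It states them twice and calls one version pre-specified, without the factors its own background describes as slowing AMD.

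**Conclusion.** The point holds in a limited form and should be corrected. The factors named for the primary adjusted model leave out centre, smoking and antioxidant supplement use, and the open-ended item does not fit a pre-specified model. If drug choice varies with any of the three after the listed adjustment, the comparison is biased and the false-positive rate exceeds 5%.

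The documents do not allow the size to be derived. The assumed scenarios give 1.0 to 4.8 points and rejection rates of 5.8% to 23.1% in an unadjusted test with no drug effect. The bias left after the planned adjustment could be smaller, and it could also hide a real effect.

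The stronger reading, that confounding alone could readily pass for the planned drug effect, is not supported. A 9-point difference of that origin would need associations of about 7.5 with both drug choice and conversion, well above the 4.75 ratio cited for fellow-eye status.

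**What to change.** 1. Replace both lists in section 2.3 by one closed list: "age, sex, baseline BCVA, AMD stage/severity, comorbidities, baseline symptom severity, and contralateral wet AMD status", with the comorbidities named, plus centre, smoking status and antioxidant supplement use. Delete the open-ended item.
2. Make sure that smoking status and supplement use are recorded at T0.
3. For conversion, bring these factors in through a propensity score, for example with overlap weighting, or through a penalised model, not as separate terms in an ordinary regression. Keep the planned clustering by participant.
4. Do not add the T0 value of an outcome as a covariate while T0 remains in the response of the repeated-measures model. The same applies to baseline BCVA when BCVA is itself the outcome.
5. Report an E-value or a similar analysis for unmeasured confounding next to the primary estimate.

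The cost is at most two baseline form items, a rewritten sentence and some added analysis work. Overlap weighting also shifts the estimate towards patients who could plausibly have received either drug, which should be stated. The sample size does not change.

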Assuming a 12% progression rate in the solifenacin group and a 3% progression rate in the mirabegron group at 12 months (absolute difference 9%), with *α* = 0.05 (two-sided) and power = 80%, the required sample size is n ≈ 134 participants per group (net, without accounting for dropouts), computed using the standard formula for comparison of two proportions. The choice of the absolute difference of 9% is not based on clinical data as no clinical trials using either solifenacin or mirabegron to verify the rate of dry AMD progression to the wet form have been performed. This absolute difference was selected as a clinically meaningful planning effect size (Number Needed to Treat ≈ 11 over 12 months). Because eligibility and outcomes are defined at the eye level and participants may contribute with one or two eligible eyes, this calculation should be considered a planning approximation; all inferential analyses will account for within-participant correlation using robust standard errors clustered by participants.

To allow for an expected 15% dropout/non-compliance rate, the enrollment target was increased accordingly, yielding n ≈ 157 participants per group (314 total). For reporting and logistical reasons this has been pragmatically rounded to 156 participants per group (312 total); the protocol will state that this figure includes an allowance for approximately 15% attrition.

The sample size was computed according to the classical formula for two independent proportions:

$$n=\frac{\left(Z_{1-\frac{\alpha }{2}}\sqrt{2p(1-p)}+Z_{1-\beta }\sqrt{p_{1}(1-p_{1})+p_{2}{\left(1-p_{2}\right)}^{2}}\right)}{{\left(p_{1}-p_{2}\right)}^{2}}$$

Where *p*_1_ = 0.12, *p*_2_ = 0.03, *p* = (*p*_1_ + *p*_2_)/2, *α* = 0.05, and 1-*β* = 0.80. The resulting net sample size is approximately n ≈ 134 per group; after adjusting for ~15% attrition the enrollment target is *n* ≈ 157per group (rounded for the protocol to 156 per group).

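### The adjusted conversion model has only about 2 to 4 events per coefficient and includes a visit with no possible events; a penalised 12-month analysis is safer

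*Protocol article*

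**What the plan says.** All of the following is in the protocol article, section 2.3 (Data analysis plan and statistical analysis), unless another place is named.

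- The study is sized on 12-month conversion: "Assuming a 12% progression rate in the solifenacin group and a 3% progression rate in the mirabegron group at 12 months". "The resulting net sample size is approximately n ≈ 134 per group". After an allowance for 15% attrition, "this has been pragmatically rounded to 156 participants per group (312 total".
- The primary outcomes, with conversion listed first, are to be analysed by mixed-effects models over T0, 6 and 12 months. The fixed effects are treatment, time and treatment×time. Adjustment covers named baseline factors and an open-ended allowance for others.
- The primary analyses are then said to use a "pre-specified adjusted model including key baseline prognostic factors (age, sex, baseline BCVA, AMD stage/severity, comorbidities, baseline symptom severity, and contralateral wet AMD status".
- Standard errors are clustered by participant. The only stated alternative to the main model applies when normality fails.
- Section 2.1 makes the eye the unit of analysis and includes both eyes when both qualify.

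The article does not state the expected number of conversions, and it names no link function or estimator for this binary outcome.

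**The concern.** A regression for a binary outcome draws its information mainly from the events. With few events per coefficient, ordinary maximum likelihood pushes coefficients away from zero. It sometimes has no finite solution, for example when one group has no event. Here the direction matters: if mirabegron works as hypothesised, the error exaggerates its benefit, in a study meant to judge whether repurposing is worth pursuing.

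The repeated-measures form adds a second difficulty. Eligible eyes have dry AMD at entry, so conversion at T0 is impossible by definition, yet T0 is one of the three modelled visits. Neither clustered standard errors nor a fallback for non-normal data deals with sparse events.

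**Working it through.** **1. The plan's own figure.** Inputs from section 2.3: p1 = 0.12, p2 = 0.03, mean p = 0.075, two-sided α = 0.05, power 80%. The usual pooled formula gives

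n = [1.960·√(2·0.075·0.925) + 0.842·√(0.12·0.88 + 0.03·0.97)]² / 0.09² = (0.730 + 0.309)² / 0.0081 ≈ 133.3, so 134 per group.

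This matches the stated 134. With attrition, 134/0.85 = 157.6, close to the stated 157.

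**2. Expected events, one eye per participant.** Evaluable: 156 × 0.85 = 132.6 per group.

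- Solifenacin: 132.6 × 0.12 = 15.9
- Mirabegron: 132.6 × 0.03 = 4.0
- Total: 19.9 (20.1 at 134 per group; 23.4 with no attrition at all)

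With 134 participants on mirabegron at 3%, the chance of no event is 0.97^134 = 1.7%, and of at most two events 23%.

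**3. Two eyes.** At 1.25, 1.5 or 2 eyes per participant, the same rates give about 25, 30 or 40 events (5, 6 or 8 on mirabegron). These events are correlated within participants.

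**4. Coefficients.** Seven named factors at one coefficient each, plus treatment, make 8. One coefficient each for time and the interaction makes 10. Time as a three-level visit factor makes 7 + 1 + 2 + 2 = 12. Several comorbidities or further factors add more.

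**5. Events per coefficient.** One eye each: 19.9/8 = 2.5; 19.9/10 = 2.0; 19.9/12 = 1.7. Two eyes throughout: 40/10 = 4.0.

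**6. Consequence for a single 12-month logistic model.** The covariate effects and prevalences below are assumptions, since the article gives none. Simulation with 134 per group, one eye each, marginal rates 12% and 3%, and 4,000 data sets per row:

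| Coefficients | True log OR | ML mean | Bias | Not estimable | Firth mean |
|---|---|---|---|---|---|
| 8 | −1.554 | −1.716 | 10.4% | 3.1% | −1.555 |
| 10 | −1.554 | −1.732 | 11.4% | 3.9% | −1.546 |
| 12 | −1.555 | −1.754 | 12.8% | 4.4% | −1.535 |

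Further simulations under other assumptions:

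- With and without confounding, 8 or 12 coefficients: maximum-likelihood bias 9.9 to 15.4%, not estimable in 2.4 to 3.5%. Firth with all covariates was within about 1%, with coverage of about 95 to 96%.
- With 16 to 25 events: bias about 7 to 10%, failure about 4 to 13%. The higher failure rates go with fewer events and with definitions that also count extreme coefficients.
- At 1.25 and 1.5 eyes per participant, treating eyes as independent: bias 9.5% and 7.4%, failure 2.6% and 0.9%. Correlation between eyes would make the true gain smaller.
- Type I error of the plain model was near 5%.
- A propensity-weighted risk difference was close to unbiased (−0.0905 against −0.0900 in one setting). The weighted odds ratio was still undefined in about 1 to 2% of data sets, when mirabegron had no event.

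**7. The repeated-measures form.** With visit as a factor, the event proportion at T0 is 0 in both groups, so the log odds there are minus infinity and contrasts with T0 have no finite estimate. Time as a straight line could give a finite slope, but one shaped by a visit at which nothing can happen. If half the conversions occur by 6 months (an assumption), the chance of no mirabegron event at that visit is 0.985^134 = 13%, which would leave the interaction there without a finite estimate too.

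**The case against.** **Estimator choice is analysis-plan detail.** The article names no estimator, and a penalised fit is compatible with its wording. This stands in part: maximum likelihood is an assumption here. But the article itself fixes the covariate list, the visits and the interaction, and it ties its only fallback to non-normality.

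**The harm is moderate.** This stands. In a nine-term simulation with a true log odds ratio of −1.60, maximum likelihood averaged −1.76, an odds ratio of 0.17 instead of 0.20. The shift of 0.16 is about a quarter of the sampling standard deviation of 0.69. Propensity weighting gave the same rejection rate as the plain model (78%), so that alternative buys no power.

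**One eye per participant is the worst case.** This also stands, and it is why a range is given. Two eyes bring more events, but they are correlated and still number at most about 4 per coefficient at ten coefficients.

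**The covariates are there for a reason.** They address confounding in a non-randomised comparison, so cutting them is no remedy. Under assumed moderate confounding, Firth regression with only treatment and contralateral status averaged about −1.35 to −1.41 against −1.60, with coverage of 88 to 92%. That is no better than the plain model's error, and in the other direction. With all nine terms, Firth gave −1.61 and 95% coverage.

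A reader might infer that the trial would have no valid primary estimate, that false positives would be inflated, or that covariates would be dropped after the data are seen. The documents do not support this. Failure is occasional, type I error is near nominal, and the model is declared pre-specified.

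**Conclusion.** The concern holds in a limited form. On the plan's own rates the conversion model has about 20 events with one eye per participant, or about 25 to 40 correlated events with many second eyes, which is about 2 to 4 per coefficient at ten coefficients. If it is fitted by ordinary maximum likelihood, expect the treatment log odds ratio to be overstated by about 7 to 15%, and no estimate in roughly 2 to 13% of data sets, depending on assumptions and on what counts as failure.

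The inclusion of T0 does not depend on simulated covariate effects: in a logistic model with visit as a factor, the time effect has no finite estimate. This does not show that the 12-month contrast itself is lost, only that the stated model is a poor vehicle for it.

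The result rests on a logistic-type model, on covariate effects that the article does not give, and, for the simulated coverage, on independent eyes.

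**What to change.** For conversion only, replace the repeated-measures model with one binary outcome at 12 months, without T0 and without the treatment×time term. This matches the endpoint in section 2.2.1 and the confirmatory timepoint in section 2.3. Fit it by Firth-penalised logistic regression with treatment and all the pre-specified covariates, naming the comorbidity terms, and cluster the inference by participant. Name the clustering method, because the coverage figures above were obtained without a second eye. The imaging outcomes can keep their mixed models.

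As a sensitivity analysis, add a 12-month risk difference with propensity (overlap) weights and participant-clustered standard errors. It uses the scale on which the study was sized. State that it targets a marginal effect in patients who could plausibly receive either drug, which differs from the conditional odds ratio; for that reason it should not silently replace the primary analysis.

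The cost is new wording, slightly more analysis work, and a point estimate slightly less favourable to mirabegron than maximum likelihood would give. Recruitment and visits do not change.

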The unit of analysis will be the eye. When both eyes meet eligibility criteria, both eyes will be included. The study will stop if severe hypertension, tachycardia, or atrial fibrillation develops; in this case, the opportunity to reduce the dose of mirabegron may be considered. The patient will have the right to withdraw their consent at any point during the study. Mirabegron displays no significant increase in major adverse cardiovascular events with a cardiovascular profile almost comparable to that of antimuscarinic agents. In our study, the safe profile of a 50 mg dosage will be associated with an increase of approximately 1 bpm for heart rate and 0.4–0.6 mmHg for systolic/diastolic blood pressure.

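### In a non-randomised study that sets out to compare safety, the only between-drug safety test is an unadjusted χ²/Fisher comparison of adverse event rates, which can mislead in either direction

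*Protocol article*

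**What the plan says.** Section 2.1 of the protocol article describes an "observational double arm non-randomized study in two centers to compare the safety and efficacy" of the two drugs, so safety is part of the comparison. The last paragraph of the Discussion likewise expects the data to show whether mirabegron reduces conversion safely as well as effectively.

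Section 2.3 treats safety in two sentences. Heart rate, blood pressure, oxygen saturation and respiratory support "will be reported as the number and percentage of patients with pathological values, without correlation to other variables"; that is description only. Then "Adverse event rates will be compared using" χ² or Fisher's exact tests. No covariates, clustering or counting unit are given for this comparison.

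Three other statements bear on it:

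- On adjustment (section 2.3): "Given the non-randomized design, primary analyses will use a pre-specified adjusted model including key baseline prognostic factors". The factors named are age, sex, baseline BCVA, AMD stage or severity, comorbidities, baseline symptom severity and contralateral wet AMD status. Secondary outcomes get the same modelling.
- On clustering (section 2.3, sample size text): "all inferential analyses will account for within-participant correlation using robust standard errors clustered by participants".
- On the unit (section 2.1): "The unit of analysis will be the eye. When both eyes meet eligibility criteria, both eyes will be included".

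**The concern.** The plan gives non-randomised treatment as its reason for adjusting the primary analyses. That reason applies equally to adverse events. If the groups differ at baseline in age, comorbidity or anything else that predicts adverse events, a crude comparison mixes that difference with any drug effect. The same baseline data are collected anyway, yet the one inferential safety analysis leaves them out.

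At stake is the safety half of the study's conclusion. A crude p-value, significant or not, could be reported as evidence that one drug is safer or that the two are alike, when it partly reflects who was prescribed which drug.

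A second, conditional issue concerns eyes. χ² and Fisher's exact tests treat every record as independent. If ocular adverse events are tabulated per eye, two eyes of one person are not independent, and the tests do not meet the clustering commitment.

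**Working it through.** **The plan's own figures.** The article states no number for the adverse event comparison. The group size used below comes from the conversion endpoint, and it reproduces. For 12% versus 3%, two-sided 0.05 and 80% power, with p = 0.075:

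- 1.96 × √(2 × 0.075 × 0.925) = 0.730
- 0.8416 × √(0.12 × 0.88 + 0.03 × 0.97) = 0.309
- (0.730 + 0.309)² / 0.09² ≈ 133.3, so 134 per group
- 134 / 0.85 = 157.6, against the stated 157, rounded to 156

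No stated number is wrong on this point.

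**Check 1: confounding.** Assumed inputs, none from the article: no drug effect, one binary risk factor, adverse event risk without it 5% or 10%, odds ratio for the factor 2 or 3. The risk with the factor is odds/(1 + odds), where odds = OR × p0/(1 − p0). The group risk is prevalence × risk with the factor + (1 − prevalence) × risk without it.

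Example: p0 = 10% and OR = 3 give odds 3 × 0.111 = 0.333 and a risk of 25% with the factor.

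- Solifenacin, prevalence 60%: 0.6 × 25% + 0.4 × 10% = 19.0%
- Mirabegron, prevalence 30%: 0.3 × 25% + 0.7 × 10% = 14.5%
- Crude risk ratio (mirabegron/solifenacin): 14.5/19.0 = 0.76, with no drug effect

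Ranges over the four combinations of risk and odds ratio, 156 per group, 200,000 simulated trials per scenario, uncorrected χ² at 1.96:

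| Factor prevalence, solifenacin vs mirabegron | Crude risk ratio | Rejection rate (nominal 5%) |
|---|---|---|
| 50% vs 50% | 1.00 | 4.8–5.0% |
| 50% vs 40% | 0.91–0.94 | 5.1–6.4% |
| 50% vs 30% | 0.81–0.88 | 5.9–10.9% |
| 60% vs 30% | 0.75–0.84 | 7.2–18.4% |
| 30% vs 50% | 1.13–1.23 | 5.8–10.8% |

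With 133 per group (156 × 0.85 = 132.6) the risk ratios are the same and the highest rejection rate is 16.5%.

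**Check 2: two eyes.** If events are counted once per participant, there is one record per person, the design effect is 1 and there is no inflation. If they are counted per eye, with a fraction f contributing two eyes and within-person correlation ρ (both assumed):

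- Design effect D = 1 + ρ × [(1 + 3f)/(1 + f) − 1]
- True two-sided error = 2 × [1 − Φ(1.96/√D)]
- f = 25%, ρ = 0.3: D = 1 + 0.3 × (1.75/1.25 − 1) = 1.12, error 6.4%
- f = 50%, ρ = 0.5: D = 1 + 0.5 × (2.5/1.5 − 1) = 1.33, error 9.0%
- f = 100%, ρ = 0.8: D = 1 + 0.8 × (4/2 − 1) = 1.80, error 14.4%

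**The case against.** Several points can fairly be made for the plan.

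- **Adjustment was never promised for adverse events.** The rule is worded for primary analyses and extends to secondary outcomes through the shared modelling. A reader might infer that the crude test contradicts the plan's own rule. It does not. What stands is that the reason given for the rule covers adverse events too.
- **The safety context is patient-level.** The sentence just before the adverse event sentence counts patients, and every listed safety parameter is systemic. The clustering commitment is introduced by a remark that eligibility and outcomes are defined by eye, so it may be meant for eye-level outcomes. A reader might combine it with "The unit of analysis will be the eye" and infer that two eyes are being ignored, or even that a systemic event would count twice. The article supports neither as a firm reading. An unstated counting unit alone is detail that an article may leave to the full protocol or SAP.
- **No direction of bias is shown.** A reader might infer that prescribing habits will make mirabegron look safer. The article describes no prescribing pattern. Table 1 applies the same cardiovascular, glaucoma and dry-eye exclusions, and the same bar on contraindications to either class, to both groups. These narrow the room for imbalance but do not close it: controlled hypertension, age and other comorbidities remain.
- **The distortion may be small.** With 50% versus 40% prevalence the rejection rate stays at 5.1–6.4%.
- **χ² and Fisher tests are customary for adverse event tables, and adjusted models are unstable with few events.** This is true, and it argues for adjusting only where counts allow. It does not justify an unadjusted test as the sole basis for a comparative safety conclusion.

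**Conclusion.** The concern holds in a limited form. The only inferential safety comparison in a non-randomised study is unadjusted, although the plan accepts non-randomisation as the reason to adjust elsewhere. That is a weakness of reasoning in a stated method.

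The size depends on assumed inputs. A moderate imbalance in a risk factor, with no drug effect, moves the crude risk ratio to about 0.75–0.88 or to 1.13–1.23, depending on which group carries the excess. The false-positive rate rises from 5% to roughly 6–18%. Either drug could be flattered.

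The conflict with the clustering commitment, and the 6–14% error that goes with it, arise only if ocular events are analysed per eye.

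**What to change.** Revise the adverse event sentence in section 2.3 as follows:

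1. Count each participant once per event type. If ocular events are analysed per eye, use standard errors clustered by participant.
2. For overall and common adverse events, report an adjusted risk difference or risk ratio with a 95% confidence interval, using the baseline factors section 2.3 already lists, including comorbidities.
3. Label the crude χ²/Fisher results descriptive.
4. Where events are too few to adjust, give counts with exact intervals and make no test-based safety claim.

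The cost is a change of wording, minor programming and wider intervals. The covariates are already part of the primary model, so sample size and visits are unaffected.

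One limit should be stated with the results. Entry requires "OAB treated for at least 6 months with either mirabegron or solifenacin", so both groups consist of people who have already tolerated their drug. Covariate adjustment does not remove that selection.
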